## **Methods**

This is a single-blinded, block-randomization controlled trial in a prospectively controlled laboratory. Sixty-six healthy university students will be recruited from the University of Sharjah, United Arab Emirates (UAE). The volunteers will be divided into three systemically randomized experimental groups. Each group will be admitted to a program of training utilizing one of three expert modes of the Russian current. The electrically elicited quadriceps muscle extensor torque

will be measured in response to modes at the participants' maximum tolerance at three points before the start of training, after three weeks of training, and at the six-week follow-up by the Biodex isokinetic system.

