## **2.5 Randomization**

Randomization will be used to determine which mode the participant will receive. The randomization sequence for our three groups of interest (Off mode, Rest mode, and On2 mode) will be computer-generated by one of the investigators who will not be involved in the volunteer recruiting the sequence will then be blocked (block sizes of 4, 6, and 8, in random order). The allocation will be hidden in sequentially numbered, sealed, opaque envelopes. The participants will be stratified by their gender (female or male).

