## **2.6 Blinding**

The study will include a random assignment for volunteers into three groups. The volunteers will be blinded, not aware of which electrical stimulation mode will be used. The examiner will know about the study because it requires practice and knowledge with an electrical stimulator. The statistician will also be blinded to intervention allocation. The data will be coded in an unrecognizable manner, with no information indicating which group a single participant will be assigned to.

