contraction, with 0 indicating "no pain" and 10 the "worst pain imaginable." Participants will be informed that a pain level of 7/10 is the maximal acceptable pain, If the pain rating reaches 7/10 or if they decide to discontinue testing for any other reason, the trials will be discontinued immediately. Similarly, the participants will be instructed to stop stimulation at a similar level of discomfort. Individuals will be submitted to the following 3 randomized test conditions, and the electrically RC elicited isometric knee extensor torque will be measured in response to each of the modes at the participants' maximum tolerance. RC stimulation session will last for 15 minutes. The Russian current neuromuscular electrical stimulation will be administered using a Chattanooga Forte 200 Combo stimulator (DJO Global, Vista, CA). The Russian currents produce 50 bursts per second at a carrier frequency of 2500 Hz, with each burst lasting 10 milliseconds and followed by a 10-millisecond inter-burst gap, resulting in a 50% duty cycle and a 200-microsecond phase duration as a fixed parameter. which automatically adjust the 3 expert modes:

OFF mode;

ON2mode; consists of two intervals the stimulus will be applied as; preset on the device, following by 2 second off and then and ON2 stimulus that has a frequency of 50 Hz and 100% amplitude.

Rest mode; consist of two intervals the stimulus will be applied as; preset on the device, then follow by a continuous Rest stimulus that has a frequency of 24 Hz and 83% amplitude.

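### The protocol contradicts itself on whether each participant is tested in one Russian current mode or in all three, which leaves the primary comparison undefined

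*Protocol*

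**What the plan says.** Most of the protocol describes a parallel-group trial. The Methods paragraph of the abstract states that "Sixty-six healthy university students will be recruited from the University of Sharjah", that "The volunteers will be divided into three systemically randomized experimental groups", and that "Each group will be admitted to a program of training utilizing one of three expert modes of the Russian current". Section 2.5 agrees: "Randomization will be used to determine which mode the participant will receive", with concealed envelopes and stratification by gender. Section 2.6 agrees too: "The study will include a random assignment for volunteers into three groups", followed by "The volunteers will be blinded, not aware of which electrical stimulation mode will be used". Figure 1 (section 2.2) shows the three modes as separate intervention rows over the same three weeks, at two sessions per week.

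Section 2.9, which sets out the testing and stimulation procedure, reads differently: "Individuals will be submitted to the following 3 randomized test conditions", and the elicited "torque will be measured in response to each of the modes" at the participant's maximum tolerance. It names no visit for this testing and does not separate test sessions from training sessions.

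The secondary objective in section 2.4 concerns discomfort under each mode condition, which fits either reading.

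**The concern.** How many modes a participant receives is a matter of design and conduct. No analysis plan can remove exposures that have already been delivered. Two examiners working from this protocol could run different trials: one measuring each person in the allocated mode, the other measuring each person in all three.

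The choice decides whether modes are compared between people or within people, and therefore which variance belongs in the error term. It also decides whether sequence, fatigue and carry-over need to be controlled. If everyone meets all three modes, the groups no longer differ only in the mode they trained with. Participants also gain a basis for telling the modes apart, in a trial where they are meant to be blinded and where discomfort is self-reported.

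**Working it through.** **Step 1. The two descriptions side by side.**

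| Question | Abstract, 2.5, 2.6 | 2.9 read literally |
|---|---|---|
| Modes per participant | one | three |
| What is randomised | the participant, to a group | the test conditions |
| Comparison of modes | between people | within people |
| Order, period, washout | not needed | needed, none given |

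The rest of the protocol does not decide between them. The word crossover is not used anywhere. Section 2.10 names descriptive statistics and a Pearson correlation, which shows neither a between-group nor a within-person comparison of modes.

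**Step 2. Does the sample size show which design was meant?** Inputs from section 2.7: difference 1.5, SD 2.5, power 80%, significance level 0.05 (two-sided assumed), dropout 10%.

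- One-sample or paired formula, with 2.5 taken as the SD of differences: (2.5 × (1.960 + 0.842) / 1.5)² = 21.8, so 22. Then 3 × 22 = 66, the stated total, but with no dropout allowance. With dropout, 22 / 0.9 = 24.4, so 25, and 3 × 25 = 75.
- Parallel two-sample formula: 2 × 21.8 = 43.6, so 44 per group and 132 in total. With dropout, 44 / 0.9 = 48.9, so 49 per group and 147 in total.

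Of the formulas tried, only a paired-type number multiplied by three groups gives 66, and that mixes the two designs. The total therefore does not resolve the contradiction. Whether 66 is adequate is a separate question and is not relied on here.

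**Step 3. Exposure to non-allocated modes.** Training is 3 weeks × 2 sessions = 6 sessions (Figure 1). Assume that each mode is tested once at a visit, so each visit adds 3 − 1 = 2 non-allocated exposures.

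- Before the week-3 assessment: 2, those at baseline.
- At the week-3 assessment itself: 2 more. These can affect that assessment only through order or fatigue within the visit.
- Over baseline, week 3 and week 6, if all-mode testing is repeated at each: 3 × 2 = 6.

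The protocol does not say at which visits all-mode testing would take place.

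**Step 4. Effect on precision.** Work in units of the between-person SD, with ρ the correlation between two modes in the same person. The protocol gives no value, so ρ = 0.5 to 0.8 is assumed. For 66 people each measured in all modes:

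- Correct paired standard error of a mode difference: √(2(1 − ρ)/66) = 0.123 at ρ = 0.5 and 0.078 at ρ = 0.8.
- Standard error if the same measurements are treated as independent groups: √(2/66) = 0.174.
- Ratio: 1/√(1 − ρ) = 1.41 at ρ = 0.5 and 2.24 at ρ = 0.8.

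The error is towards intervals that are too wide, so real differences between modes would be missed. In the other direction, if each person has only one mode, there are no pairs and a paired model cannot be fitted.

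**The case against.** The strongest reply is that parallel allocation is stated again and again, while the within-person reading rests on one loosely worded sentence. That sentence could mean that participants, taken together, are spread over three randomised conditions. This reading is possible, and it is a good reason to treat the parallel design as the intended one. It does not remove the problem: nothing in section 2.9 confirms it, and measuring torque in response to each of the modes is within-person wording in the section that describes the procedure.

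Several stronger readings should be resisted:

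- A reader might infer that the trial is crossover and parallel at once and cannot be validly analysed as either. That does not follow. If each person gets one mode, a between-group analysis is valid. If all modes are tested but one is trained, the randomised training groups can still be compared, and pre-training torque can be compared within person with order and period terms.
- A reader might compare 22 against 22 in parallel, √(2/22) = 0.302, with 0.123 to 0.078 and conclude that a wrong model distorts the error by 2.4 to 3.9 times. Those are two different data sets. The ratio includes a factor of √3 (66 against 22 people) that has nothing to do with choosing the wrong model.
- A reader might count four non-allocated exposures by week 3. Two of those occur during the week-3 assessment, so only two can carry over into it.
- A reader might infer that blinding is broken. Section 2.9 describes modes that differ on paper, so recognition is plausible, but the document does not show that participants could identify their mode.

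It is also fair to say that the authors must decide whether they want an acute within-person comparison. The fix leaves that open.

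**Conclusion.** The contradiction is real and must be reconciled before testing starts. The abstract and sections 2.5 and 2.6 give each participant one mode. Section 2.9, read literally, tests each participant in all three, without an order, period or washout. Until this is settled, the unit of comparison and the error term of the primary outcome are undefined.

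The contradiction itself rests on the text alone. The sizes rest on assumptions: two non-allocated exposures before week 3 requires each mode to be tested once at baseline, and a standard error 1.4 to 2.2 times too large requires 66 people measured in all modes, analysed as independent, with a within-person correlation of 0.5 to 0.8. Order and fatigue effects and weaker blinding are possible consequences, not demonstrated ones.

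**What to change.** Reconcile section 2.9 with the parallel design stated elsewhere. Say that torque at each assessment is measured in the participant's allocated mode and that modes are compared between the randomised groups. Remove the wording that submits individuals to three conditions and measures torque under each mode. In the secondary objective of section 2.4, refer to discomfort in each group instead of under each mode condition. State in section 2.9 which procedures belong to assessment visits and which to training sessions.

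If an acute within-person comparison is intended, describe it as a separate component, with its visit, a randomised mode order and a paired analysis, and keep it apart from the training comparison.

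The cost is protocol wording, and testing time does not rise. The downside is that the within-person acute comparison is either dropped or has to be specified in its own right.

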## **2.10 Statistical analysis and power**

For the statistical analysis of the information gathered, the SPSS 22.0 software (SPSS Statistics Ink, 176 Chicago, IL, USA) for Windows will be used. For the variables being examined,

frequency, mean, and standard deviation will be computed, as will the median and interquartile range.

The initial data will be collected from the participants before starting the program and then during the program on the 3rd and 6th weeks. For the data analysis regarding each participant, we will be using Pearson correlation (r).

The data that will be obtained from this study is a description statistic, where the mean and standard deviation of measured variables will be calculated, and inferential statistics will be used to calculate the Pearson correlation (r) to examine the EIT quadriceps muscle strength in association with the three continuous variables.

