## **Hypothesis**

We hypothesize that electrically induced torque of the quadriceps muscle in healthy persons will be differently affected by various Russian current modes.

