### **Primary outcome measure**

Considering the potential advantages of NMES for enhancing muscle performance and the dearth of research in this area, the main objective of this study will be directed to evaluate the impact of various Russian current expert modes on the maximum electrically induced torque of the quadriceps femoris, and to compare the electrically elicited knee extensor torque at the maximal stimulation tolerance level using 3 different RC experts' modes (off mode, on mode and on2 mode).

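### The only inferential method the protocol states, a Pearson correlation with three unidentified continuous variables, cannot compare torque between three randomised modes

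*Protocol*

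**What the plan says.** The Hypothesis section states that "electrically induced torque of the quadriceps muscle in healthy persons will be differently affected by various Russian current modes". In section 2.4, the primary outcome paragraph sets out "to compare the electrically elicited knee extensor torque at the maximal stimulation tolerance level using 3 different RC experts' modes". Section 2.5 randomises participants to Off, Rest or On2, stratified by gender. Section 2.7 bases the sample size on a mean difference of 1.5 with a standard deviation of 2.5.

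Section 2.10 promises descriptive statistics ("frequency, mean, and standard deviation will be computed, as will the median and interquartile range") and one inferential tool, Pearson's r. It appears twice: once for the data of each participant, and once as "the Pearson correlation (r) to examine the EIT quadriceps muscle strength in association with the three continuous variables". Neither section 2.10 nor any other part of the protocol says which three variables are meant. No test, model or contrast between the modes appears anywhere in the document.

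**The concern.** The protocol asks whether three groups differ in mean torque, then commits itself to a measure of linear association between continuous variables. Mode is a nominal factor with three levels, so it is not one of three continuous variables. Followed literally, section 2.10 would yield correlation coefficients but no estimate, interval or test of the effect of mode, and the hypothesis could be neither supported nor refuted. It would also leave the test that does answer the question to be chosen later, possibly with the data in view.

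**Working it through.** **Step 1: what the rest of the protocol requires.**

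| Element | Where | What it implies |
|---|---|---|
| Torque affected differently by mode | Hypothesis | difference between modes |
| Compare elicited torque across three modes | 2.4, primary outcome | difference between modes |
| Random allocation to Off, Rest or On2 | 2.5 | nominal factor, three levels |
| Mean difference 1.5, SD 2.5 | 2.7 | comparison of means |
| Pearson r with three continuous variables | 2.10 | linear association only |

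The first four agree with each other. The fifth does not fit them.

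**Step 2: the possible readings of the three variables.**

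- *Time points, or participant measures such as age, BMI or maximal voluntary torque.* The correlation contains no contrast between modes and makes no use of the randomisation.
- *Torque under the three conditions, correlated with one another within person.* Correlation is unchanged if a constant is added to one variable. Two modes could correlate perfectly and still differ widely in mean torque, so r does not test the difference.
- *Mode, entered as codes 1, 2, 3.* The result depends on which mode receives which code (step 3).

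**Step 3: illustration for the coded reading.** Inputs: planned difference 1.5 and SD 2.5 (section 2.7), so 1.5/2.5 = 0.6 SD. Assumptions: equal groups, one mode 0.6 SD above the other two, within-group variance 1.

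- Variance of the codes 1, 2, 3: 2/3.
- Variance of the group means (0.6, 0, 0): 0.36/3 - (0.2)² = 0.12 - 0.04 = 0.08, so the total outcome variance is 1.08.
- Covariance if the differing mode is coded 3: (+1 × 0.6)/3 = 0.2. If coded 1: -0.2. If coded 2: (0 × 0.6)/3 = 0.
- r = covariance / √(2/3 × 1.08) = ±0.2/0.8485 = ±0.236 at either end, and 0 in the middle.

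The same data therefore give three answers. A simulation with 22 per group (66/3, equal allocation assumed; 4,000 runs) shows the consequence. Pearson's test at 0.05 rejects in 4.6% of runs when the differing mode is coded 2, no more than its false-positive rate, and in about 50% when it is coded at an end. The one-way ANOVA F test rejects in about 52% under any coding (51% by exact calculation).

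**Step 4: what the stated analysis could detect.** By Fisher's z with 66 participants, 80% power and two-sided 0.05 (sidedness assumed), the smallest detectable correlation is tanh((1.960 + 0.842)/√63) = 0.34. No objective in the protocol is expressed in that quantity.

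**The case against.** The strongest defence is that a statistical analysis plan may exist and may contain a proper comparison of the modes. That limits the wording: one may say that no method stated in this protocol tests the primary objective, but not that the trial will never test it. It does not remove the point, because section 2.10 is not silent. It fixes a method that cannot answer the question, and a later plan with a group comparison would have to depart from it.

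A reader might infer more than the document supports:

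- *That Pearson's r will be run on mode codes.* The protocol does not say so. Step 3 illustrates one reading of an undefined phrase.
- *That the baseline maximal voluntary torque (KEMVIT) is ignored.* Section 2.9 uses it to normalise elicited torque to %KEMVIT.
- *That failing to model repeated visits, gender strata or covariates is itself an error.* Such detail is commonly left to an analysis plan. Section 2.5 also gives no reason for stratifying by gender, so nothing can be claimed about how strongly gender affects the outcome.
- *That baseline adjustment would bring a large gain in power.* The documents give no correlation between voluntary torque and tolerance-limited elicited torque. If the outcome is %KEMVIT, strength has already been divided out and the correlation could be near zero.

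**Conclusion.** The stated primary inference is wrong as written and must be replaced. This rests on the text alone: one method, unidentified variables, and an objective that the method cannot address under any reading. The coding example (r of 0, +0.24 or -0.24 from the same data) shows how badly one reading fails; it assumes equal groups and a single mode differing by the protocol's own 0.6 SD.

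The conclusion does not depend on whether 66 participants are enough, which is a separate question, nor on any assumed benefit from covariates.

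**What to change.** In section 2.10, replace the Pearson analysis as the primary inference. Compare elicited torque between modes on one stated scale (Nm or %KEMVIT, section 2.9) at one named primary time point; section 2.4 lists both three and six weeks without choosing. Fit an ANCOVA or a mixed model with allocated mode as a three-level factor, adjusted for gender as the stratification factor. Report the overall two-degree-of-freedom test, then the pairwise differences with 95% confidence intervals. Keep Pearson's r as descriptive only, and name the variables it uses.

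If the scale is Nm, KEMVIT measured before stimulation can be added as a covariate. Its gain is unknown. For a 0.6 SD difference and 20 per arm (22 less 10% dropout, rounded), t-test power with the SD multiplied by √(1 - r²) is as follows, every r being an assumption:

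| Assumed r | 0 | 0.3 | 0.5 | 0.7 | 0.8 |
|---|---|---|---|---|---|
| Pairwise power | 46% | 49% | 57% | 73% | 87% |

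Before the model is fixed, section 2.9 must be reconciled with the rest. It speaks of individuals undergoing three randomised test conditions, with torque measured under each mode, whereas the abstract's Methods and section 2.5 describe parallel groups with one mode each. A within-person design would need a different model.

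The cost is a rewritten section 2.10 and decisions on outcome scale, primary time point and the design wording. No new data are required.

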### **3.Discussion**

#### **3.1 Potential study impact and significance**

Russian currents (medium-frequency alternating currents) are frequently utilized in rehabilitation and to enhance athletes' muscle performance, even though a lot of research has demonstrated a dose-response connection in which higher evoked muscle torques lead to stronger improvements, Analyzing NMES parameters separately can yield useful clinical data on how to effectively employ NMES to achieve strength training in people with and without injury. The expert mode is one such parameter that has been poorly studied. Electrical stimulation parameters such as phase duration, pulse duration, duty cycle, carrier frequency, and waveform type have been studied in the past. [4,14,16,25-30] However, no one addresses the effect of the RC expert mode on the quadriceps muscle in a healthy individual. The findings of this study protocol may be useful for

physiotherapists and their patients, as they could have the potential to utilize the most effective parameters when the goal is to produce maximum knee extensor torques with less discomfort.

### **3.2 Future research**

Future research could use the protocol's findings to examine whether the results are consistent across different muscle types and patient demographics.

### **3.3 Study strengths and weaknesses**

The current study has some limitations. The hamstring muscle group will not be explicitly observed during this procedure. The net torque of the knee extension may decrease due to the hamstrings contracting. The anterior thigh's tissue thickness makes it extremely unlikely that the current would have reached the hamstring muscles. Another limitation of this study is that this trial will only be performed on healthy volunteers' quadriceps femoris muscles. Therefore, future research will be recommended to see if the results of the current study would be similar in other muscles and patient populations.

